## Abstract

**Background:**

Adherence to antiretroviral therapy (ART) is essential for allowing persons living with HIV to live longer, healthier lives. However, a large portion of this population has suboptimal adherence and are not virally suppressed. Conventional interventions aimed at improving ART adherence lack portability and scalability, and improvements in adherence are not often sustained. Mobile health (mHealth) ART interventions offer a low-cost and accessible method of improving adherence, but many have limited functionality and do not offer comprehensive support. The combination of an mHealth intervention with a face-to-face adherence intervention and interactive health coaching feature may offer sufficient support in a manner that is sensitive to resource limitations that are often found in HIV treatment settings. This paper details the protocol of a study designed to evaluate the potential of an enhanced mHealth intervention for improving ART adherence.

**Objective:**

The primary objective of this study is to assess the feasibility and acceptability of the Fitbit Plus app enhanced with a face-to-face LifeSteps session (Fitbit Plus condition) for improving ART adherence. In addition, we will determine the preliminary efficacy of the intervention by calculating treatment effect sizes.

**Methods:**

This study will be conducted in 2 phases. The intervention will be developed and piloted with a small group of participants during phase 1. Pilot participants will provide feedback that will be used to refine the intervention for phase 2. In phase 2, a preliminary randomized controlled trial (RCT) comparing Fitbit Plus with a condition that approximates the standard of care (SOC) will be conducted with 60 persons living with HIV. Interviews will be conducted with RCT participants at baseline, and follow-up interviews will be conducted at 1, 3, 6, and 12 months. ART adherence is the primary outcome and will be monitored throughout the study via electronic pill boxes. Effect sizes will be generated using a fractional logit model estimated by generalized estimating equations.

**Results:**

Phase 1 of this trial is complete; data collection for phase 2 is ongoing. Follow-ups with enrolled participants will conclude in January 2020.

**Conclusions:**

This study will contribute to the literature on ART adherence and may produce an efficacious intervention. Owing to a small sample size, there may be insufficient power to detect statistically significant differences between Fitbit Plus and SOC. However, if Fitbit Plus is found to be acceptable and feasible and yields promising effect size estimates, this pilot study could serve as the foundation for a larger, fully powered trial of Fitbit Plus.

**Trial Registration:**

ClinicalTrials.gov NCT02676128; https://clinicaltrials.gov/ct2/show/NCT02676128

**International Registered Report Identifier (IRRID):**

DERR1-10.2196/15356

## Introduction

### Background

The Centers for Disease Control and Prevention estimates that 1.1 million people living in the United States are infected with HIV [1], with an estimated 38,739 new HIV diagnoses in 2017 alone [2]. Antiretroviral therapy (ART) is highly effective and allows persons living with HIV (PLWH) to live longer, healthier lives [3,4]. Despite the effectiveness of ART, only 60% of PLWH living in the United States achieve viral suppression [5]. Medication nonadherence is a significant contributor to unsuccessful viral suppression; a meta-analysis found that only an estimated 59% of participants in North American studies were adherent at the commonly accepted minimal threshold for successful viral suppression of 90% [6]. Although newer medications can produce viral suppression at lower levels of adherence, relatively high adherence is still necessary to avoid disease progression and shortened lifespan [7-9].

Given the significant public health problem presented by poor adherence to ART, a great deal of research has been devoted to improving adherence. Interventions have been developed to address poor ART adherence, with most studies demonstrating some degree of success [10]. LifeSteps, one of the early interventions in this area, is a single session intervention that incorporates motivational interviewing, cognitive-behavioral skills, and problem-solving components and is grounded in the Information-Motivation-Behavioral Skills Model of ART adherence [11-13]. It was found to improve adherence more rapidly when compared with a self-monitoring condition [12] and has been used in conjunction with cognitive behavioral therapy (CBT) interventions to improve ART adherence and reduce depressive symptoms in PLWH [11,14,15]. A noted shortcoming of ART adherence interventions is the tendency of their treatment effects to diminish over time [10]; most real-world clinical settings lack the resources necessary to sustain any adherence improvements that are achieved [10].

To address concerns of portability and sustainability of improvements from traditional ART adherence interventions, effort has also been directed at the development of mobile health (mHealth) ART adherence interventions. mHealth ART interventions allow greater accessibility than clinical settings and provide a low-cost option for continued intervention. To date, the bulk of the research in this area has focused on text message–based ART adherence interventions. A meta-analysis of text messaging interventions [16] found fairly modest but significant support for these interventions. However, most of the interventions examined were of short duration, which is noteworthy given the well-known challenges of habituation and response fatigue with these types of interventions.

Currently, there are hundreds of HIV-related mHealth apps marketed for PLWH on either Android or Apple platforms. Fortunately, a number of mHealth apps for PLWH have been found to be effective, as well as feasible and acceptable [17]. However, most current mHealth interventions have limited functionality, such as only offering medication reminders [17]. Another review highlighted key content areas that are not currently addressed by existing apps: resources regarding psychological and emotional support and components that enhance linkage to treatment providers [18]. Therefore, more comprehensive mHealth interventions, which address multiple self-management needs of PLWH, are needed.

Evidence suggests that treatment supporters result in better adherence to ART [19]. Examples of treatment supporters include peer support sessions, home visits by nurses or counselors, case management, and provision of training in treatment support to a friend or family member of the patient. The importance of this type of adherence support has been found in other reviews as well [20,21].

Health coaches represent one type of treatment supporter. Health coaching has a patient-centered focus, involving patients in the process of goal setting [22]. Health coaches assist the patient in achieving a greater understanding of the patient’s medical condition and encourage patient accountability [22]. Reviews of the general literature regarding health coaching conclude that the approach shows great promise for improving health outcomes [23,24].

### Objective

One particular smartphone app that has shown promise in improving ART adherence incorporated personalized health-related information with medication reminders [25]. This paper outlines the protocol behind a study designed to extend and enhance this previous work. These enhancements include a face-to-face adherence intervention and an interactive health coaching feature, which were selected to address barriers and limitations of typical mobile adherence aids. At the conclusion of the study, we will be able to determine the feasibility, acceptability, and preliminary efficacy of this intervention.

## Methods

### Overview

To assess the feasibility, acceptability, and preliminary efficacy of the study intervention, we will develop and test the intervention through 2 phases. In phase 1, we will pilot and refine our face-to-face intervention and the use of our smartphone app (Fitbit Plus). In phase 2, we will conduct a randomized controlled trial (RCT) of 60 PLWH to examine the effect of the face-to-face intervention followed by Fitbit Plus (Fitbit Plus condition) compared with the face-to-face intervention alone, which approximates standard of care (SOC condition) in most HIV treatment settings. Participants in the RCT will complete a baseline interview and follow-up interviews at 1, 3, 6, and 12 months. The primary outcome will be ART adherence based on electronic pill box (EPB) data.

### Participants and Recruitment

A total of 80 PLWH (n=20 in phase 1 and n=60 in phase 2) will be recruited from the Northeast region of the United States via community advertisement and in-person recruitment at an outpatient HIV treatment center. Persons will be eligible for the study if they are at least 18 years of age, have been prescribed ART, are living with HIV, have had a detectable viral load (>20 copies/mL) within the past 6 months, report less than 100% self-reported medication adherence, and have a smartphone that is compatible with Fitbit Plus. Persons living with physical or cognitive impairment that could impede completion of the intervention or jeopardize informed consent, active psychosis, or who are not fluent in English will be excluded from participation. This study has been reviewed and approved by the first author’s institutional review board.

After receiving a description of the study from research staff, anyone interested in participating will be asked to complete a screening interview. The screening interview, which will include a review of medical information, will assess eligibility and will be used to ensure no exclusion criteria are met. Demographic information, including age, gender, time since HIV diagnosis, mode of HIV transmission, and type of cell phone used will be collected as a part of the screening interview. For screening purposes, a single-item visual analog scale [26] will be used to measure ART adherence for the past month. In this measure, respondents are asked to rate percentage of prescribed doses taken in the past month on a visual analog scale ranging from 0% to 100%. We will confirm the absence of cognitive impairment using the University of California, San Diego Brief Assessment of Capacity to Consent measure [27] and the absence of active psychosis using the Mini-International Neuropsychiatric Interview (MINI) [28], with positive responses to the MINI further queried by doctoral-level study staff. Written informed consent will be obtained from those who are eligible; this will be obtained at the time of the screening interview for those who are screened in person or during the first in-person visit for those who are screened over the phone.

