#### Viral Load

Viral load data will be collected at baseline and at the 6- and 12-month follow-up appointments. These data will be collected through a laboratory belonging to a hospital system in the Northeastern region of the United States. The laboratories use assays with sensitivity to detect viral load >20 copies/mL.

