### Planned Analyses

Tests of the effects of treatment on the primary outcome variable (percent ART adherence based on corrected EPB data at 1-, 3-, 6-, and 12-month follow-ups) will be conducted using a fractional logit model [56] estimated by generalized estimating equations (GEEs) [57-59]. GEE is a quasi-likelihood estimation method of repeated measures analysis that allows for the inclusion of both categorical and continuous independent variables and for appropriate modeling of covariance structures when outcomes are correlated across time. The primary, between groups, independent variable in the above regression analysis is treatment group assignment. Variables measured at baseline will be examined using screening runs before primary analyses to see which of these baseline variables are most strongly associated with the primary outcome (adherence based on EPB data) in our sample. Those that show significant relationships with outcome will be entered as additional covariates in the primary analyses. The linear effect of time will also be included as a covariate in these analyses, as we assume that adherence rates will show a tendency to decrease over time. We will also test for nonlinear (ie, higher order) effects of time. Testing the time by group interaction will indicate the extent to which treatment differences are more or less pronounced closer in time to the intervention.

The same process described above for EPB adherence data will be employed to examine the impact of Fitbit Plus, relative to SOC, on the secondary measures of self-reported adherence percentage and viral load (dichotomized). Changes in viral load test assays have created inconsistencies in the literature in regard to level of viral load that is detectable. To be able to compare our results with the extant literature, we will dichotomize viral load at the 3 most commonly used levels (20, 50, and 200 copies/mL) and examine intervention effects using each of these levels. We will then explore potential mediators (motivation and self-efficacy) of the intervention effect on HIV medication adherence. This will be done using 2 common approaches to evaluating mediation mechanisms; Baron and Kenny’s approach [60] and structural equation modeling [61,62].

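### Baseline viral load is measured, but it enters the viral load models only if a significance screen selects it, although participants may enter already below a cut-off

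*Protocol article*

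**What the plan says.** **Entry** (Protocol article, Participants and Recruitment). Applicants must "have had a detectable viral load (>20 copies/mL) within the past 6 months" and "report less than 100% self-reported medication adherence". The section states no requirement on the current viral load.

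**Measurement** (Viral Load). "Viral load data will be collected at baseline and at the 6- and 12-month follow-up appointments". On the assay: "The laboratories use assays with sensitivity to detect viral load >20 copies/mL".

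**Outcome** (Planned Analyses). Viral load is one of the "secondary measures of self-reported adherence percentage and viral load (dichotomized"), and the authors state that "we will dichotomize viral load at the 3 most commonly used levels (20, 50, and 200 copies/mL"), so that results can be compared with the literature.

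**Model** (Planned Analyses). "The same process described above for EPB adherence data will be employed to examine the impact of Fitbit Plus". For the primary outcome, that process screens the baseline variables for association with pill-box adherence and adds those found significant as covariates. Baseline viral load is not named as a term that enters regardless.

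**Allocation** (Phase 2, Procedures). The urn uses years on ART, visual analog adherence, substance use and depressive symptoms. Viral load is not among them.

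**Aim and size** (Results, Discussion). The target is 60 participants, and 53 had been randomised at the time of writing. The authors say that power may be inadequate and that the purpose is an effect size that can support a larger trial.

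**The concern.** The entry threshold equals the lowest outcome cut-off, and the qualifying value can be up to six months old. Someone who qualified at 21 to 49 copies/mL was already below the 50 and 200 cut-offs. Someone at 50 to 199 was already below 200. Either may be at or below 20 by the study baseline. Follow-up status at a cut-off therefore mixes people who can gain suppression with people who can only keep or lose it, and baseline status is likely to predict follow-up status strongly.

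Neither design nor analysis secures that predictor. The urn does not balance it, and a significance test in a small sample decides whether it is in the model. If the screen is rerun for each outcome, it may be selected at one cut-off and not at another. If the covariates chosen for pill-box adherence are carried over, it may be missing from all three models. The text allows both readings. What is at stake is how far the viral load effect size can be trusted and compared across cut-offs. Viral load is the only efficacy outcome that depends on neither the pill box nor self-report.

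**Working it through.** The article gives no suppression rate, effect size or power for viral load, so there is no stated figure to reproduce. All rates below are assumptions. Let f be the share below a cut-off at baseline.

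**1. Chance imbalance.** Inputs: N = 53 (Results); simple 1:1 allocation (assumed; the ratio is not stated, and the urn variables may reduce imbalance somewhat if they correlate with viral load). The SD of the between-arm difference in baseline status is √[f(1 − f) × 4/N].
- f = 0.5: √(0.25 × 4/53) = 0.137, about 14 points.
- f = 0.3 or 0.7: √(0.21 × 4/53) = 0.126, about 13 points.
- N = 60, f = 0.5: √(0.25 × 4/60) = 0.129, about 13 points.

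Assume follow-up suppression of 40% in those above the cut-off at baseline and 90% in those below. With no treatment effect, an imbalance d moves the unadjusted difference by (0.90 − 0.40)d, so one SD at f = 0.5 gives 0.5 × 13.7 = 6.9 points. If the app raises 40% to 60% and leaves 90% alone, the gap is 0.30 in one arm and 0.50 in the other. The shift is then 0.40d, or 5.5 points, against a pooled effect of 0.5 × 20 = 10 points.

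**2. Would the screen catch it?** Approximate power of a two-sided 5% test of baseline status against follow-up status in 53 people is Φ[(|p1 − p2| − 1.96 s0)/s1], where s0 and s1 are the pooled and unpooled standard errors.
- 40% vs 90%, f = 0.5: (0.50 − 1.96 × 0.131)/0.112 = 2.18, power about 98%.
- 50% vs 75%, f = 0.5: (0.25 − 1.96 × 0.133)/0.128 = −0.08, power about 47%. The one-SD shift with no treatment effect is then 0.25 × 13.7 = 3.4 points.
- 40% vs 90%, f = 0.1: (0.50 − 1.96 × 0.228)/0.148 = 0.36, power about 64% (rough, with about 5 people below the cut-off).

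The screen would almost surely select a very strong, evenly split predictor. It is close to a coin toss for a moderate one and uncertain for a lopsided one.

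**3. Comparability across cut-offs.** With a logit link, adjusted and unadjusted odds ratios differ even without imbalance. Suppose the odds ratio is 3.50 in both baseline groups: 30% to 60% above the cut-off, and 85% to 95.2% below it (odds 5.67 × 3.50 = 19.83). At f = 0.4 the pooled rates are 0.6 × 0.30 + 0.4 × 0.85 = 0.520 and 0.6 × 0.60 + 0.4 × 0.952 = 0.741. The unadjusted odds ratio is (0.741/0.259)/(0.520/0.480) = 2.64. Adjusting at one cut-off and not at another would put the three odds ratios on different scales.

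**4. Does pooling shrink the effect?** Pooled difference = (1 − f) × (effect on gaining) + f × (effect on keeping). With gaining at 30% vs 60%:

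| Keeping, control vs app | f = 0.2 | f = 0.4 | f = 0.6 |
|---|---|---|---|
| 85% vs 85% | 0.24 | 0.18 | 0.12 |
| 70% vs 90% | 0.28 | 0.26 | 0.24 |
| 60% vs 90% | 0.30 | 0.30 | 0.30 |

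Shrinkage depends on the effect on keeping. Restricting to those above the cut-off does not always help. With 27 per arm (90% of 30) and f = 0.4, power is 40% restricted against 27% pooled in the first row, but 40% against 49% in the second.

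**The case against.** A reader might go further and infer that many participants enter suppressed and that the pooled analysis therefore hides a virological effect. The documents do not support this. They show that such entry is possible, not how often it happens. They never define the outcome as gaining suppression: a randomised comparison of the proportion below a cut-off is a valid effect in the enrolled population, and a larger trial with the same entry rule would need that effect. All entrants report imperfect adherence, so an effect on keeping suppression is plausible, and the shrinkage in step 4 disappears when that effect is as large as the effect on gaining.

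A reader might also infer bias from recent ART starters whose viral load is falling anyway. Years on ART is an urn variable, so such falls should be roughly balanced between arms and add noise rather than bias.

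The remaining defence is that viral load is secondary, that the authors already warn of low power, that the screen could select baseline viral load, and that an article may leave model detail to an analysis plan. The first three points stand and limit the weight of this one; step 2 shows that a very strong, evenly split predictor would very probably be selected. The last does not fully answer it. The article is not silent: it states a selection rule and applies it to viral load, and that rule does not secure the baseline value of the outcome.

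**Conclusion.** The point holds as one of analysis, not of eligibility. Participants may enter below the 50 or 200 cut-off, or even the 20 cut-off, and the stated rule leaves adjustment for baseline viral load to a significance screen. Under the assumed rates, a one-SD chance imbalance moves the unadjusted difference by roughly 3 to 7 points. The larger shifts at an even split are those the screen would usually catch; the smaller ones it would miss about half the time. Differing adjustment would also make the three odds ratios hard to compare.

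These sizes rest on assumed suppression rates, an assumed share below the cut-off and simple 1:1 allocation. The pooled comparison is valid, no stated figure is wrong, and the primary pill-box outcome and the sample size are untouched.

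**What to change.** In Planned Analyses, name baseline viral load as a fixed covariate in each viral load model, whatever the screening runs show. Use baseline status at the same cut-off, or the log10 value where that status is too sparse, as may happen at 20 copies/mL.

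As description only, tabulate follow-up suppression by arm separately for participants above and below each cut-off at baseline, with confidence intervals. This shows whether any difference comes from gaining or from keeping suppression.

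Leave eligibility unchanged. A sensitivity analysis on the timing of the qualifying value relative to ART start is not worth adding: the article does not say that the date of that value is recorded, and any definition of recent ART start would be arbitrary.

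Cost: one extra model term and some tables from data already collected. The baseline strata will be small and their intervals wide. According to Results, formal analysis follows the end of data collection, so the wording can be fixed beforehand.

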### Phase 1: Development and Piloting Phase

#### Procedures

During phase 1, we will test the face-to-face adherence intervention followed by the use of Fitbit Plus with 5 to 10 PLWH. In-depth interviews will be conducted with these pilot participants after they have used Fitbit Plus for 3 months, in addition to brief phone interviews after 1 month of Fitbit Plus use, to gain an understanding of the strengths and limitations of the app as well as to garner feedback regarding the face-to-face session content. This feedback will guide refinement, and this process will then be repeated with another 5 to 10 PLWH. To enhance follow-up rates, participants in phase 1 will be paid US $50 for completing the postintervention interview. The data collected from these participants regarding feasibility, acceptability, and barriers or challenges that would limit effectiveness will guide modifications to the intervention.

#### Face-to-Face Antiretroviral Therapy Adherence Intervention

Our single session face-to-face ART adherence intervention will be based on the LifeSteps intervention [11,12,14,15]. Consistent with the literature regarding efficacious adherence interventions [21,29], LifeSteps combines brief motivational interviewing, CBT, and problem-solving skills and is grounded in the IMB Skills Model of ART adherence [13]. During the development phase of the study, Fitbit Plus orientation material will be added to the face-to-face intervention that will be delivered to pilot participants and to RCT participants assigned to the Fitbit Plus condition. The introduction to Fitbit Plus will include downloading the app to the participant’s phone, entering the participant’s ART medication schedule, and assisting the participant in formulating an ART adherence goal, which will be entered into the app so that both the patient and health coach can track progress toward the goal. Participants who do not have password protection enabled on their phones will be encouraged to activate this feature to protect the privacy of their information. During the orientation to Fitbit Plus, we will highlight that the interactive coaching feature is not intended for use in medical or other emergencies and that side effect and other medical questions should be directed to clinic treatment providers. Pilot participant feedback will guide refinement of the face-to-face intervention, including the Fitbit Plus orientation content, during phase 1 of the study.

